### **C. Sample size, statistical methods, and power calculation**

1. Descriptive statistics (frequency/percent and mean/SD) will be mainly used to summarize participants' characteristics and intervention outcomes. The means and 95% CIs for pre-post changes in the primary (i.e., frailty index) outcome will be estimated. No imputation will be considered for missing data. The Wilcoxon rank sum test will be used for comparing the pre-post changes in frailty index between the two groups. The intervention will be considered feasible if the retention rate and the proportion of completed sessions are more than 80%. Pre-generated randomization codes will be prepared by the biostatistician ([name]). The randomization ratio will be 1:1.
2. [name], who will be the assessor for the study assessments, will be blinded to which group the participants have been allocated to. Participants will be aware of which group they are in. The study coordinator and [name] will have access to the code to the blind. The code will not need to be broken unless there are unforeseen circumstances in which [name] needs to know which group a particular participant was assigned to. Following the baseline assessment (visit 2), participants will be randomized to one of the two groups based on pre-generated randomization codes prepared by the biostatistician, [name]. In accordance with the CONSORT guidelines, sequence generation, allocation concealment and group allocation will be blinded and separate processes.
3. For this pilot study, we plan to enroll a convenience sample of 60 ambulatory people (30 per group) with Multiple Sclerosis living with frailty that meet inclusion/exclusion criteria. These subjects will provide feasibility data and preliminary efficacy data for designing a future study if the findings are promising. We expect a 15% dropout rate, and at that at least 24 subjects per group will complete the study.

**D. Subject Criteria (See Vulnerable Populations appendix, if applicable):** We will enroll 60 ambulatory pwMS living with frailty. During Visit 1, we will screen subjects for frailty based on established cut-offs according to the Fried phenotype. This screening tool was chosen to ensure a time- and cost-effective identification of pwMS who are frail.

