Once participants meet the screening criteria, they will attend the first study assessment (Visit 2 – baseline assessment). During this visit, participants will undergo the blood draws in the morning, in fasting conditions (i.e., at least 12 hours of fasting), at the Landon Center on Aging (laboratory tests listed in Table 1 – see biomarkers). After the blood draw, participants will complete a comprehensive battery of physical and cognitive tests, self-reports, clinical measurements, and nutritional status measures (see Table 1) in the Human Performance Laboratory at the Landon Center on Aging. These procedures will take about 90 minutes. At the end of the visit, they will be provided with a wearable sensor consistent with our previous work. From these assessments, we will derive 70 health-deficit items that will be used to calculate a frailty index according to the guiding principles of the deficit accumulation model. A synopsis of the frailty index is provided in Table 1. The health-deficit items will be coded on a 0-1 scale, to indicate the absence or presence of health deficits, using standard validated procedures by a single researcher experienced in frailty assessments and blinded to group allocation (PI [name]). The frailty index score will be calculated as the

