sum of all deficit-related scores divided by the sum of the total number of possible health deficits. The same procedures will be repeated during the post-intervention assessment (Visit 3). During the screening visit and visit 3, participants will complete two pain questionnaires and a pain threshold test. First, participants will complete the Paindetect, a screening tool of neuropathic pain (one of the most common pain pwMS) and the Fibromyalgia Survey Criteria (a proxy measure of nociplastic pain). Then, participants will undergo a pressure pain threshold involving the middle part of bulk of medial and lateral gastrocnemius muscles as well as the thumbnail of the participant's dominant hand. This is measured with a digital algometer, which has been shown to have good reliability in the gastrocnemius region. The digital algometer is made up of a 1-cm-wide disk located on the middle part of bulk of medial and lateral head of gastrocnemius muscles. The algometer's pressure will be increased gradually (with a speed approximately 1 N/cm^2 per second) and will be stopped immediately when the participant reports the transition from discomfort to pain. The average value of three measurements will be recorded.

**Table 1.** Synopsis of the 70-item frailty index: Domains, sources and measures utilized as health deficit items.

| Domains of frailty             | Items, number | Sources                                           | Measures                                                                                                                                                                      |
|--------------------------------|---------------|---------------------------------------------------|-------------------------------------------------------------------------------------------------------------------------------------------------------------------------------|
| Global health                  | 2             | MSQoL-54                                          | self-reported health.                                                                                                                                                         |

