| Function in ADLs               | 6             | MSQoL-54                                          | Questions about the ability to perform ADLs                                                                                                                                   |
| Energy                         | 5             | MSQoL-54, MFIS                                    | Questions about tiredness, energy, and fatigue                                                                                                                                |
| Psychosocial function          | 6             | MSQoL-54, MFIS                                    | Questions about participation in social activities, feelings of happiness, downheartedness, etc                                                                               |
| Health attitudes/sleep quality | 6             | Wearable sensor (worn for three consecutive days) | Number of daily steps, number of 30-seconds walking bouts, moderate to vigorous physical activity, total physical activity, number of hours spent sleeping, sleep efficiency. |
| Cognition                      | 6             | CVLT-II, SDMT, BVMT, TMT, MFIS                    | Total words recalled, Total BVMT score, Raw SDMT score, TMT times, self-reported memory problems.                                                                             |
| Physical performance           | 6             | Instrumented gait analysis, 6MWT, Dynamometry     | Self-selected gait speed, functional ambulation profile, 6MWT distance, handgrip strength, knee extensor strength, 5X chair stand.                                            |
| Nutritional status             | 5             | Laboratory tests, Self-report.                    | BMI, serum albumin, appetite disorders, problems with cooking.                                                                                                                |
| Comorbidities                  | 16            | Medical records, Automated BP monitor, MSQoL-54.  | Polypharmacy, systolic BP, diastolic BP, comorbidities; fall history                                                                                                          |

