| Biomarkers                     | 12            | Laboratory tests                                  | NfL, BDNF, GFAP, CRP, IL-6, IL-10, TNF-alpha, IFN-gamma, and CXCL9, mi-RNAs.                                                                                                  |

**Legend:** ADL: activities of daily living, MSQoL-54: 54-item multiple sclerosis quality of life questionnaire, MFIS: modified fatigue impact scale, CVLT-II: California verbal

learning test, SDMT: symbol digit modalities test, BVMT: brief visuospatial memory test; TMT: trail making test, 6MWT: 6-minute walk test, BP: blood pressure, BMI: body mass index, CRP: c-reactive protein.

All study outcomes will be assessed in a standardized manner during Visit 2 and 3. Following visit 2, participants will be randomized to one of the two groups based on pre-generated randomization codes prepared by the biostatistician. In accordance with the CONSORT guidelines, sequence generation, allocation concealment and group allocation will be blinded and separate processes. Participants will then either complete the waitlist period (passive control) or attend the exercise training visits 3 times a week, for 6 weeks, totaling 18 training visits. Each training visit will last one hour. The training visits will take place at the Laboratory for Advanced Rehabilitation Research in Simulation at the University of Kansas Medical Center.

**Intervention (Multimodal exercise) Group:** Participants will complete 15 minutes of virtual reality treadmill training (VRTT), followed by 30 minutes of progressive evidence-based resistance training (RT), followed by other 15 minutes of VRTT. This interval training design was chosen to induce acute fatigue before the last bout of VRTT. See Table 2.

**Table 2.** The Multimodal exercise program.

| Exercise components      | Duration   | Description                                                                                                                    | Target (frailty domains)*             |
|--------------------------|------------|--------------------------------------------------------------------------------------------------------------------------------|---------------------------------------|
| 1) VR treadmill training | 15 minutes | Treadmill walking with interactive virtual environment.                                                                        | - Slowness
- Cognition             |

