| 2) RT                    | 30 minutes | Seated leg press, seated hamstring curls, seated calf raises, seated chest press, seated lat-pulldowns, seated shoulder press. | - Muscle weakness
- Shrinkage      |
| 3) VR treadmill training | 15 minutes | Treadmill walking with interactive virtual environment.                                                                        | - Slowness, Cognition
- Exhaustion |

**Legend:** VR: virtual reality, RT: resistance training, \* The multimodal exercise program will also inherently target the 'inactivity' component of frailty.

Both the VR and RT components of the program will be individualized based on the participant's abilities and the training progression will be adjusted every 2 weeks. Over-ground gait speed will be assessed prior to the intervention and every two weeks thereafter and will be utilized to set the treadmill speed for the VR component. As part of VR, participants will navigate through a virtual environment projected on a TV screen while receiving feedback from the system (Figure 2). The RT component will consist of performing evidence-based RT exercises, as fully described in Table 2. In the event participants are unable to complete 15 minutes of continuous walking, walking duration will be progressively increased in 1–3-minute bouts until the prescribed time is reached. The estimated 1-repetition maximum (1-RM) of all RT exercises will be evaluated using validated standard procedures (for untrained individuals) prior to the intervention. At the beginning of the intervention, participants will complete 3 sets of 8-12 repetitions at 20-30% of the 1RM and slowly progress up to 80% over the course of 8 weeks. The end point of each set will always be limited to volitional fatigue. Recovery periods of 2-4 minutes will be prescribed between sets and exercises.

**Control Group:** Participants randomized to the control group will be put on a waitlist (passive control group) for 6 weeks. Upon completion of Visit 3, participants in the control group will be able to receive the intervention, if they wish so.

[figure not shown]

Panel A

[figure not shown]

Panel B

Figure 2. Gait Better (TM) virtual reality (VR) treadmill training set up. Panel A. Camera detects markers on feet and projects them on screen. Panel B. View of VR monitor depicting individual's virtual feet, visual distractors, and obstacles.

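### The three-day sensor wear behind 6 of the 70 frailty-index items is not tied to allocation or the start of training, so baseline values can be recorded after the arm is known

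*Protocol*

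**What the plan says.** Protocol II.E.2 (Study Procedures) describes Visit 2 as the baseline assessment and closes it with the sensor hand-out: "At the end of the visit, they will be provided with a wearable sensor". Table 1 gives the source for the health attitudes/sleep quality domain as "Wearable sensor (worn for three consecutive days" and lists six measures: "Number of daily steps, number of 30-seconds walking bouts, moderate to vigorous physical activity, total physical activity, number of hours spent sleeping, sleep efficiency". These belong to the primary frailty outcome, since from the Visit 2 assessments "we will derive 70 health-deficit items that will be used to calculate a frailty index".

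Randomization is placed twice. II.C.2 says "Following the baseline assessment (visit 2), participants will be randomized to one of the two groups", and II.E.2 says "Following visit 2, participants will be randomized to one of the two groups based on pre-generated randomization codes". II.E.2 then moves directly to the waitlist or to training three times a week for six weeks. II.C.2 also states that participants are not blinded.

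For follow-up, II.E.2 says "The same procedures will be repeated during the post-intervention assessment (Visit 3", and the control-group paragraph says "Upon completion of Visit 3, participants in the control group will be able to receive the intervention, if they wish so".

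No sentence says when the sensor comes back. None makes randomization, its disclosure, the first training session or control access to training depend on completed wear.

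**The concern.** A baseline value should be fixed before the participant knows the allocation. Data from a sensor issued as a visit ends do not exist until about three days later, and the protocol's next step after that visit is randomization of unblinded participants. A site could follow the text exactly and collect baseline steps, walking bouts, activity and sleep from people who already know whether they are training or waiting, or who have had a first session.

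The overlap can act directly. Each session contains two 15-minute treadmill walks, which a sensor could register as steps, bouts and physical activity. At follow-up, a control who begins the intervention straight after Visit 3 could add the same kind of activity to the follow-up record.

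The analysis compares pre-post change in the index between arms, so either overlap enters the comparison. A pre-allocation baseline cannot be reconstructed afterwards. The protocol also intends to use the resulting effect sizes to power a later trial, so a distortion would carry forward.

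**Working it through.** **1. Reproduce the index size.** The Table 1 domain counts are 2 + 6 + 5 + 6 + 6 + 6 + 6 + 5 + 16 + 12 = 70, which agrees with the stated 70 items. The sensor supplies 6 of them: four activity items (daily steps, 30-second walking bouts, moderate-to-vigorous activity, total activity) and two sleep items.

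**2. Put the sequence in order.**

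| Step | What the protocol fixes | What it leaves open |
|---|---|---|
| Baseline sensor | Given at the end of Visit 2; three days of wear (II.E.2, Table 1) | Return date |
| Randomization | After Visit 2; participants know their arm (II.C.2, II.E.2) | Whether wear must be finished first |
| First session | After randomization; three sessions a week (II.E.2) | Any gap after allocation |
| Follow-up sensor | Visit 2 procedures repeated at Visit 3 (II.E.2) | Explicit hand-out and return times |
| Control access | From completion of Visit 3 (II.E.2) | Whether completion includes the wear |

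II.E.2 also says that all outcomes are assessed during Visits 2 and 3. That does not fit a three-day recording that starts as a visit ends, so the text does not place the wear in the sequence.

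**3. Size the exposure.** With items scored 0 to 1, the index shift for one participant is (items changed)/70.

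- One item: 1/70 = 0.0143
- Two items: 2/70 = 0.0286, below 0.03
- Three items: 3/70 = 0.0429, above 0.03
- Four activity items: 4/70 = 0.0571
- All six sensor items: 6/70 = 0.0857

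The 0.03 threshold (II.B, Aim 2) equals 0.03 × 70 = 2.1 items.

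**4. Translate to a group mean.** If m affected items shift by an average of s on the 0–1 scale in one arm only, the mean index difference moves by m × s / 70. To move it by 0.03:

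- m = 6: s = 0.03 × 70 / 6 = 0.35
- m = 4: s = 0.03 × 70 / 4 = 0.525

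So the timing alone would have to shift the sensor items in one arm by an average of about a third of their full range, or about half if only the activity items moved. Smaller shifts would distort the comparison without reaching the threshold.

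**5. What cannot be computed.** The protocol gives no standard deviation of index change and no power target, and nothing in it says how far the sensor items would move. The effect on the Wilcoxon comparison therefore has no basis in the document.

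**6. Room for a delay.** II.E.5 allows 2.5 months per participant: 2.5 × 52/12 = 10.8 weeks. Less 6 weeks of training, about 4.8 weeks remain for the other steps.

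**The case against.** The best defence is that this rests on silence. II.C.2 places randomization after the baseline assessment, the sensor is issued within that assessment, and the 70 items are derived from it. On that reading the wear is part of the baseline, and randomization naturally waits for it. This is a fair reading, and it defeats any claim that the protocol requires wear after allocation. It does not remove the point: II.C.2 itself equates the baseline assessment with Visit 2, the sensor is handed over only as that visit ends, and no text holds allocation for its return. Both readings are open to a site.

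The follow-up overlap is less likely. A control would have to opt in and begin within about three days of Visit 3, and the program requires gait-speed and one-repetition-maximum testing before training. The hand-out at Visit 3 is itself inferred from the repetition of procedures. The spare weeks in the participant window also make a first session inside the baseline wear less likely. These arguments lower the probability of overlap but do not exclude it.

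A reader might also treat follow-up wear after training has stopped as a fault. It is not one: a post-intervention measure should follow the intervention, and wear during training would count treadmill sessions as daily activity.

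Finally, a reader might take 0.086 as the expected bias, or assume that the bias runs toward zero. The figure needs all six items to move across their full range. Early sessions in the exercise arm or early training in controls would shrink the apparent effect, but reactions to knowing the allocation could go either way.

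**Conclusion.** The point holds as a sequencing gap: the protocol permits, but does not require, baseline wear after allocation is known or training has begun, and it permits control follow-up wear to overlap training. The baseline part is the stronger. The follow-up part assumes that the sensor is issued at the end of Visit 3 as at Visit 2, and that a control starts quickly.

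The step 3 shares are theoretical maxima for the affected items, and 70 − 6 = 64 items are untouched. They are large enough to matter because three fully changed items take a participant past the clinical threshold. No net bias or direction can be derived from the document.

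The order of measurement, allocation and treatment is a protocol procedure and cannot be repaired in the analysis, so it should be settled here. Severity is moderate: this is a pilot with a convenience sample of 60, a feasibility aim first and an efficacy aim that is only exploratory.

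**What to change.** In II.E.2, with matching wording in II.C.2:

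- State that randomization, or at least its disclosure to the participant, and the first training session occur only after the three-day baseline wear is complete and the sensor has been returned.
- State that the follow-up sensor is issued at Visit 3 in both arms, and define completion of Visit 3 to include the follow-up wear, so that no control starts the intervention before it ends.
- Reword the sentence that places all outcomes within Visits 2 and 3 so that it allows for the wear periods.

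For anyone already randomized, record the dates of wear, disclosure and first session. If overlaps occurred, a supporting analysis on the 64 non-sensor items would show whether they matter.

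The cost is a few days' delay per participant at each end, which fits within the roughly 4.8 weeks of slack, plus a rule for a participant who does not return the sensor before randomization. No assessment is added and the sample size is unchanged.

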#### **E. Specific methods and techniques used throughout the study**

1. **Laboratory tests:** Participants will be asked to complete a blood draw, in fasting conditions (in the morning), during study visits 2 and 3. The blood draws will be performed by a trained nurse at the Landon Center on Aging. The blood drawn will be done to assess biomarkers that are correlates of frailty such as NfL, BDNF, GFAP, CRP, IL-6, IL-10, TNF-alpha, IFN-gamma, and CXCL9, mi-RNAs. The amount of blood drawn will be approximately 12-15 mL.
2. **Study Procedures:** Participant involvement in this study will begin with the screening visit, where subjects will be screened for eligibility using objective diagnostic criteria. The screening visit will take place at the KU Center for MS Care and will take about 10-15 minutes. At the screening visit, participants will go through the informed consent with a study team member. If the participants consent, they will then complete the Mini-Cog questionnaire and the Fried phenotype to determine if they meet the frailty criteria. The Fried phenotype evaluates 5 components: fatigue, weakness, ambulation, inactivity, and loss of weight. Fried scores range from 0-5 (i.e., 1 point for each component). Higher scores reflect higher frailty. Subjects who total at least 3 points out of 5 will be classified as frail and will be eligible to participate. The Fried phenotype will also be repeated after the intervention, during Visit 3.

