**G. Location where study will be performed:** The screening visit will be performed at the KU Center for MS Care. The assessments (visits 2 and 3) will be performed in the Landon Center on Aging. The training visits will be performed at the laboratory for Advanced Rehabilitation Research in Simulation at KUMC.

**H. Collaboration (with another institution, if applicable):** N/A

**I. Single IRB Review for a Multi-site study (if applicable):** N/A

**J. Community-Based Participatory Research (if applicable):** N/A

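### The protocol gives two schedules for the pain measures, and under the specific one baseline and follow-up pain are taken under different conditions, which confounds the within-arm before/after change

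*Protocol*

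**What the plan says.** Section I.A sets an exploratory aim with two parts. One compares pain between frail and non-frail people with MS. The other looks at pain before and after training, with the hypothesis that the exercise arm improves more than the control arm.

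Section II.E.2 gives the pain schedule: "During the screening visit and visit 3, participants will complete two pain questionnaires and a pain threshold test". The instruments are painDETECT, the Fibromyalgia Survey Criteria and a pressure pain threshold at the medial and lateral gastrocnemius and the thumbnail. After Table 1 the same section gives a general rule: "All study outcomes will be assessed in a standardized manner during Visit 2 and 3".

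The visits differ in content:

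- Screening: "The screening visit will take place at the KU Center for MS Care and will take about 10-15 minutes".
- Visits 2 and 3, place (II.G): "The assessments (visits 2 and 3) will be performed in the Landon Center on Aging".
- Visits 2 and 3, blood (II.E.1): "Participants will be asked to complete a blood draw, in fasting conditions (in the morning), during study visits 2 and 3". Section II.E.2 sets the fast at 12 hours or more.
- Visit 2, order: "After the blood draw, participants will complete a comprehensive battery of physical" tests and further assessments, about 90 minutes in all. Visit 3 repeats these procedures.

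Randomization follows Visit 2. Only people scoring at least 3 on the Fried phenotype at screening go on to Visit 2.

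**The concern.** Section II.D identifies screening as Visit 1, so the two statements name different baseline visits for pain. This is a question of data collection, and an analysis plan cannot settle it afterwards: if pain was not measured at Visit 2, a baseline under Visit 3 conditions cannot be recovered once the participant has been randomized.

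Under the specific statement, the two pain measurements differ in site, visit length, fasting and blood draw. Visit 3 also contains the 6-minute walk, the five-times chair stand and knee extensor strength (Table 1). These load the legs, and the calf is one of the places where the pressure threshold is tested. The protocol does not say whether the pain tests come before or after them.

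At stake is the before/after pain change in each arm. A single-arm change, or an effect size built from it, would combine any real change with the effect of measuring under other conditions and over a longer, variable interval.

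**Working it through.** The protocol states no sample size, power or error rate for pain, so there is no figure to reproduce. The check has two parts.

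**1. The two baselines side by side**

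| | Screening (Visit 1) | Visit 2 | Visit 3 |
|---|---|---|---|
| Pain, specific statement (II.E.2) | yes | not named | yes |
| Pain, general rule (II.E.2, after Table 1) | not named | yes | yes |
| Site | KU Center for MS Care | Landon Center on Aging | Landon Center on Aging |
| Fast and blood draw | none described | yes | yes |
| Physical battery | none described | yes | yes |
| Place of pain tests in the visit | not stated | not stated | not stated |

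Visits 2 and 3 match on every row that describes conditions. Screening and Visit 3 do not.

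No window is set between screening and Visit 2. The timeline in II.E.5 allows 2.5 months per participant, which is 2.5 × 52/12 = 10.8 weeks. Taking off the 6-week period leaves 10.8 − 6 = 4.8 weeks for everything else. That is a planning figure, not a limit, but it shows that the interval from screening to Visit 3 can be well above 6 weeks and can vary between people.

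**2. What a change of conditions does to each estimate**

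Inputs: 24 completers per arm (II.C.3). Assumptions: pain changes are normal with SD 1; there is no treatment effect; the same shift *s* is added in both arms; the test is two-sided at 5%. The Wilcoxon rank sum test, which the protocol names for the frailty index, is applied to pain. The documents give no size for *s*, so a range is shown. Results are from 3,000 simulated trials per row.

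| Shift *s* (SD) | Mean within-arm change | Within-arm 95% CI excludes 0 | Mean between-arm difference | Rank sum test rejects |
|---|---|---|---|---|
| 0 | 0.00 | 5% | 0.00 | 5.3% |
| 0.25 | 0.24 | 21% | −0.01 | 4.9% |
| 0.5 | 0.50 | 64% | 0.00 | 4.8% |
| 1.0 | 1.00 | 99.5% | 0.00 | 4.6% |

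The within-arm column can be checked directly. The one-sample t statistic has noncentrality *s*√24, which is 1.22, 2.45 and 4.90. With 23 degrees of freedom this gives 22%, 65% and 99.7%, in line with the simulation.

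*Precision.* If the changed conditions also add independent noise with SD *e*, the SD of change becomes √(1 + *e*²): 1.03 for *e* = 0.25 and 1.12 for *e* = 0.5. Assume a true between-arm effect of 0.8 SD and 24 per arm. By the normal approximation, power = Φ(0.8 / (SD × √(2/24)) − 1.96):

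- *e* = 0: Φ(2.77 − 1.96) = 0.79
- *e* = 0.25: Φ(2.69 − 1.96) = 0.77
- *e* = 0.5: Φ(2.48 − 1.96) = 0.70

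**The case against.** The strongest reply is that the trial is randomized and the intervention hypothesis for pain compares the arms. Both arms have the same screening visit, the same unfixed gap and the same Visit 3, so a common shift cancels. This stands, and the table above shows it. It rests on the shift being the same in both arms, and nothing in the documents suggests otherwise. What remains exposed is the single-arm change, which the aim also sets out to explore.

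A second reply is that pain is measured at screening for a reason: it is the only visit attended by both frail and non-frail people. This also stands. It justifies a screening measurement but does not make that measurement a good baseline for change.

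A third is that the general rule follows the frailty index table and may have been meant only for those items. That reading is possible, but the sentence covers all study outcomes and promises standardized assessment. Even if it is accepted, the difference in conditions between the two pain visits remains.

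A reader might go further in three ways that the documents do not support:

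- *That Visit 3 pain is tested after exertion.* The protocol orders the battery after the blood draw but does not place the pain tests. Only the missing order can be criticized.
- *That the Fried score has the same defect, worsened by selection.* It is true that "The Fried phenotype will also be repeated after the intervention, during Visit 3", and the screening score selects participants. But Fried is the eligibility screen, no analysis of Fried change or reversal is planned, and the named frailty outcome is the frailty index at Visits 2 and 3.
- *That the stated screening length is too short for the pain tests.* Any such estimate needs assumed thresholds and pauses, and no result depends on it.

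**Conclusion.** The concern holds in limited form. The two statements in II.E.2 conflict for pain and must be reconciled. Under the screening-and-Visit-3 schedule, the within-arm before/after pain change carries a visit-condition effect whose size and direction cannot be known from the documents. If it were 0.25 to 0.5 SD, a within-arm interval based on 24 people would exclude zero in about 21% to 64% of trials with no real change.

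The between-arm comparison is not biased by a shift common to both arms. Its cost is precision: on the assumptions above, power falls from 0.79 to between 0.77 and 0.70.

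The point is minor. It concerns an exploratory aim in a pilot, and the frailty index is unaffected. It is still worth correcting, because the correction is cheap and a Visit 2 pain value cannot be obtained later.

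**What to change.** Reconcile the two statements in II.E.2 as follows:

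1. For people who go on to be randomized, measure pain at Visit 2, before randomization, and at Visit 3. Fix the same point in both visits, before the physical battery.
2. Name these two values as the basis for pain change, within and between arms.
3. Keep the screening pain measurement and use it for the frail versus non-frail comparison, because non-frail people do not reach Visit 2.

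The cost is a change of wording and an estimated 10 to 20 more minutes at Visit 2, which the general rule in II.E.2 already implies. Participants who are later randomized would do the pain tests three times instead of twice.
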